### CCTA Scanning Protocols

All CCTA acquisitions will be performed in each medical center using CT scanners with ≥64 detector rows. A non-contrast enhanced coronary calcium scoring study will be obtained before the CCTA examination. The specific scanning protocols are consistent with the routine clinical practice of CCTA in each medical center. Nitroglycerin and beta-blockers will be administered according to the standard practice of each center. Baseline scanning characteristics will be obtained through an electronic questionnaire for each participating patient after CCTA examination, such as scanning equipment, scanning protocols, the name, concentration, dosage and injection rate of iodinated contrast agent, average heart rate during scanning, and the usage of nitroglycerin and beta-blockers. All the Digital Imaging and Communications in Medicine (DICOM) files will be transferred to the core laboratory online or offline for image quality and coronary stenosis assessment after the initial screening in each center. After double-checking the data, subjects who meet the inclusion criteria will be finally enrolled and informed by the core laboratory.

### Coronary Plaque Evaluation

The coronary artery is divided into 17 segments according to the American Heart Association (AHA) classification (24). The right coronary artery (RCA) includes segments 1, 2, 3, 4, and 16. The left main (LM) and left anterior descending (LAD) include segments 5, 6, 7, 8, 9, and 10. The left circumflex (LCX) includes segments 11, 12, 13, 14, and 15. Coronary plaques will be identified in segments with a diameter ≥1.5 mm. Lesions located in the major epicardial coronary arteries will be classified as proximal (segments 1, 6, and 11), middle (segments 2 and 7), and distal (segments 3, 8, and 13).

#### Evaluation of the Coronary Plaque Calcification

To quantify coronary plaque calcification, the Agatston score (AS) will be calculated for each patient by multiplying the calcified lesion area by the maximum density of a single target lesion in this area using a semiautomated software (SyngoVia, Siemens Healthineers, Forchheim, Germany) (25). Based on the AS, patients will be divided into four groups: 0, 1–99, 100–299, and ≥300 (26). In addition, we will evaluate the degree of plaque calcification of the most severe lesion using the arc of calcification in the short axis. Accordingly, the degree of target lesion calcification is defined as: (1) no calcification (no calcification present); (2) mild (<90°arc calcification); (3) moderate (90–180°arc calcification); (4) severe (180–270°arc calcification); or (5) very severe (270–360°arc calcification) (27).

#### Quantitative Evaluation of the Coronary Plaque

Quantitative plaque analysis will be performed by a group of observers using a semiautomated software (QAngioCT, Medics, Leiden, The Netherlands). The following plaque parameters will be assessed: %DS (degree of lumen stenosis calculated at the site of maximal stenosis, defined as 100% × [reference diameter-minimal lumen diameter, MLD]/reference diameter); plaque length; MLD and minimal lumen area (MLA); plaque volume (defined as vessel volume minus lumen volume), such as the total volume, the volume of calcification components (>350 HU), lipid components (<30 HU), fiber-fatty components (30–130 HU) and fibrous components (131–350 HU) (28); plaque burden (PB) (defined as 100% × [plaque volume/vessel volume]); and the remodeling index (RI) (automatically calculated), calculated as the diameter, i.e., both plaque and vessel lumen at the site of maximal stenosis divided by the mean diameter of the proximal and distal reference site. Plaque volume and burden will be summed on a per-segment, per-vessel, and per-patient level. According to the RI, lesions will be categorized into three groups as follows: positive remodeling (PR; RI > 1.0), negative remodeling (RI < 0.88), and intermediate remodeling (0.88 ≤ RI ≤ 1.0).

On a per-lesion basis, CAD-RADS categories are defined as follows: CAD-RADS 1 (1–24% stenosis or present coronary plaque without apparent stenosis), CAD-RADS 2 (25–49% stenosis), and CAD-RADS 3 (50–69% stenosis). On a per-segment/vessel/patient basis, CAD-RADS categories will be evaluated based on the maximal stenosis. According to the AHA classification, the number of segments ≥1.5 mm diameter with any calcified, non-calcified, or mixed plaque will be recorded, regardless of the degree of stenosis, for the calculation of segment involvement score (SIS). The maximum SIS value that can be derived is 17 for each patient. A comprehensive CTA risk score will be calculated using an online calculator (http://18.224.14.19/calcApp/) according to the previous study (29). The CCTA risk score is derived from CONFIRM registry, and the calculated content includes the presence, location, extent, severity, and composition of CAD.

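### Plaque burden is defined as a ratio of volumes but is then to be summed, so the vessel or patient value is not a burden by the plan's own definition and can exceed 100%

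*Protocol article*

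**What the plan says.** The section Quantitative Evaluation of the Coronary Plaque gives two definitions and one aggregation rule.

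- Volume: "plaque volume (defined as vessel volume minus lumen volume").
- Burden: "plaque burden (PB) (defined as 100% × [plaque volume/vessel volume"]).
- Aggregation: "Plaque volume and burden will be summed on a per-segment, per-vessel, and per-patient level".

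The article nowhere says that burden is recomputed from totalled volumes, averaged or weighted. The same section does choose a different rule for another measure: "On a per-segment/vessel/patient basis, CAD-RADS categories will be evaluated based on the maximal stenosis". It also plans a separate count of segments with plaque, the segment involvement score (SIS): "The maximum SIS value that can be derived is 17 for each patient".

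Under Coronary Plaque Evaluation, the tree is split into 17 segments, and "Coronary plaques will be identified in segments with a diameter ≥1.5 mm". Neither section says whether plaque-free segments enter the vessel or patient value.

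**The concern.** Plaque volume is vessel volume minus lumen volume, so it can never exceed vessel volume. Burden computed as defined therefore lies between 0 and 100% for a lesion, a segment, a vessel or a whole patient. The aggregation rule breaks this bound, because a sum of ratios with different denominators is not the ratio of the sums.

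Burden is a listed quantitative plaque parameter. The second aim in the Introduction is the predictive value of CT-FFR beyond clinical and anatomical factors. The Data Analysis section plans Cox models for variables against MACE, ROC cut-offs for quantitative data and comparisons of AUC between models. If summed burden enters any of these, its hazard ratio per point and its cut-off are on a scale that is not plaque burden. They could not be compared with results from studies that use the ratio. Several observers will do the readings, and the sentence allows them or the analysts to implement different versions.

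**Working it through.** The plan states no figure on this point, so there is nothing to reproduce. The check applies the plan's own definition.

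**Inputs from the article.** Burden for segment i: PBᵢ = 100 × Pᵢ/Vᵢ, with P plaque volume and V vessel volume. Aggregation as written: S = ΣPBᵢ. Aggregation by the definition: B = 100 × ΣPᵢ/ΣVᵢ. Up to 17 segments can contribute.

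**Inputs assumed.** Segment volumes and burdens, and the number of diseased segments; the article gives none of these.

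**1. Values above 100%.** Segments of 300, 200 and 100 mm³ with burdens of 50%, 45% and 40%:
- plaque volumes 150 + 90 + 40 = 280 mm³; vessel volume 600 mm³
- S = 50 + 45 + 40 = 135%
- B = 100 × 280/600 = 46.7%

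In general S passes 100% once the mean burden over k segments exceeds 100/k: 50% for two segments, 33.3% for three, 25% for four and 20% for five.

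**2. Dependence on segmentation.** Take one 600 mm³ vessel with a uniform burden of 45%. Read as 1, 2, 3 or 5 segments, S = 45%, 90%, 135% or 225%. B is 45% each time, and the plaque has not changed.

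**3. Segment size is ignored.** One 300 mm³ segment at 70% holds 210 mm³ of plaque and scores S = 70. Four 100 mm³ segments at 30% hold 4 × 30 = 120 mm³ and score S = 4 × 30 = 120. The patient with less plaque in the measured segments gets the higher value.

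Steps 1 to 3 follow from the definition; the assumed values only illustrate it.

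**4. How far S departs from B across patients.** This needs assumptions, and the answer turns on which segments are included.

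*Diseased segments only* (20,000 simulated patients per scenario; mean burden 40 or 50%, SD 8 to 15 points; 1 + Poisson(1.5 to 5) diseased segments; 0 or 49% of burden variance between patients):
- the number of diseased segments explains 62 to 97% of the variance of S
- pooled burden explains 2 to 33%
- 43 to 98% of patients exceed 100%

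*All of 13 segments, plaque-free segments at 0 or 30%:*
- R² of S with the number of diseased segments is 0.95 or 0.75
- R² of S with pooled burden is about 0.81
- 87 to 100% of patients exceed 100%

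*Another set of inputs* (about 4 diseased segments, SD 2.2; mean burden 38%, SD 8 between and 8 within patients; correlation of extent and burden 0 to 0.5):

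| Segments included | Spearman, S with B | Top tertile by S also in top tertile by B |
|---|---|---|
| Diseased only | 0.36 to 0.65 | 48 to 64% |
| Fixed 13 or 16, plaque-free at 0, 15 or 30% | about 0.96 to 0.98 | about 88 to 92% |

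So the ranking of patients may be badly distorted or almost preserved. The scale is wrong in both cases.

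**The case against.** **Loose wording in a condensed article.** The authors may mean that volumes are totalled at each level and the ratio is then applied. That is plausible and may be what will be done. But the sentence names burden as a thing to be summed, and nothing else in the article corrects it. This is a stated rule that conflicts with the definition beside it, not a detail left to a fuller document.

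**The damage is limited.** This stands. Total plaque volume is validly summed and remains available, as do component volumes, lumen measures, CAD-RADS, SIS, the CTA risk score, the Agatston score and the high-risk plaque features. The error can be reversed from the recorded volumes.

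**Stronger readings that a reader might infer, and that the article does not support:**
- *Summed burden mainly counts diseased segments, or reverses the order of patients.* This depends on pooling over diseased segments alone. Three segments at 25% sum to 75 and one at 60% sums to 60, against pooled values of 25% and 60%. Over 13 equal segments with the rest at 0, the pooled values are 75/13 = 5.8% and 60/13 = 4.6%, the same order as the sums. If the number of analysable segments varies between patients, agreement would be lower than with a fixed tree.
- *Values up to 17 × 100% = 1,700%.* That needs zero lumen throughout the tree. Eligibility requires maximal stenosis below 50% in the left main and below 70% elsewhere.
- *CT-FFR's added value is inflated by a weak comparator.* The article names no model covariates, other anatomical terms are collected, and the simulations contain no outcome and no CT-FFR.

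**Conclusion.** The aggregation rule for plaque burden is wrong as written. That rests on the article's own definition and needs no assumption: the summed value is unbounded by 100%, ignores segment size and changes with the number of segments read (135% against 46.7% in the example). A hazard ratio or cut-off for it cannot be interpreted as plaque burden.

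The size of the practical effect is not determined by the article. Under assumed inputs, the rank correlation with pooled burden runs from 0.36 to 0.98, depending mainly on whether plaque-free segments are counted. An effect on the comparison with CT-FFR is possible but not demonstrated.

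The primary endpoint, eligibility, the CT-FFR definition and the sample size are untouched. This is a minor to moderate correction of one derived predictor.

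**What to change.** Replace the aggregation sentence with:

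> Plaque volumes and vessel volumes will be summed per segment, per vessel and per patient over all analysed segments ≥1.5 mm in diameter; plaque burden at each level is 100% × (summed plaque volume)/(summed vessel volume) over those same segments.

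If a version restricted to diseased segments is also reported, label it as such, because it carries less information on extent. Apply the same rule to component burdens if they are reported.

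The cost is one sentence, agreed before the plaque data are derived. The definition of burden already requires both volumes wherever it is measured, so those segments need no new reading. The one thing to confirm is that vessel and lumen volumes are also recorded in plaque-free segments, which the article does not say. If they are not, either record them or report the diseased-segment version under its own name.

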#### Qualitative Evaluation of the Coronary Plaque

According to previous studies, four signs of coronary artery plaques on CCTA will be recorded as HRP features, namely, low-density plaque (LAP), PR, punctate calcification (SC), and napkin ring sign (NRS) (26). LAP is defined as the plaque component with an attenuation of <30 HU. RI > 1 indicates PR. SC is defined as any discrete calcification less than or equal to 3 mm in length and occupying less than or equal to 90° arc when viewed in the short axis. NRS is recognized as a central low attenuation plaque with a peripheral rim of higher attenuation of the non-calcified plaque.

### CT-FFR Measurements

All CT-FFR values will be calculated by using an automated software (“Shukun-FFR” software from Shukun [Beijing] Technology Co., Ltd). The “Shukun-FFR” software consists of two main components, the coronary arteries segmentation model and the computational fluid dynamics (CFD) simulation model. Specifically, a modified V-Net is first used to to segment coronary arteries from the CCTA image firstly (30). Then, we adopt prior knowledge to name vascular branches based on additional anatomical rules, using previous vessel segmentation results as input. The final reduced-order CFD model is applied to compute the flow and pressure of blood and calculate CT-FFR values automatically for all points along coronary arteries. CT-FFR values will be determined for coronary arteries ≥1.5 mm in diameter in the core laboratory by two cardiovascular radiologists (observers A and B). The automatically identified coronary plaques and the degree of lumen stenosis will be verified by another well-experienced observer. Observer A will carry out measurements two times separately (recorded as A1, A2). The time interval between the two measurements is 2 weeks to eliminate the effect of memory; observer B will measure one time (recorded as B). CT-FFR values will be measured at the proximal, distal, and 20 mm distal to the stenosis and the end of the target vessel (at least 1.5 mm diameter). CT-FFR ≤ 0.80 indicates the hemodynamic significance of coronary stenosis. Patients with CT-FFR ≤ 0.80, which is 20 mm distal to the stenosis, are deemed to have lesion-specific ischemia. Patients without lesion-specific ischemia but with CT-FFR ≤ 0.80 at the end of the target vessel are deemed to have distal vessel ischemia.

### Endpoints and Definition

Outcomes will be ascertained by phone contact with the patient (or family member if needed), reviewing medical records or consulting with the attending physicians, if possible, and adjudicated blindly by an independent clinical event committee according to ACC/AHA standards and the fourth universal definition of MI by reviewing symptoms, cardiac laboratory biomarker data, electrocardiogram results, and cardiovascular imaging findings (31, 32).

### Primary Endpoints

The primary endpoint is the occurrence of MACE at follow-up, defined as a composite of all-cause death, non-fatal MI, unplanned revascularization (at least 60 days after the CCTA examination), and hospitalization for unstable angina. Death cases consist of cardiovascular death, non-cardiovascular death, and undetermined cause of death. Cardiovascular death includes death attributable to sudden cardiac death, acute MI, heart failure, cardiovascular bleeding, stroke, cardiovascular procedure, and other cardiovascular causes, such as pulmonary embolism. When a definite non-cardiovascular cause is documented, a cardiovascular reason for death could be excluded. Non-fatal MI consists of ST-segment elevation myocardial infarction (STEMI) and non–STEMI. Unstable angina is defined as the symptoms of ischemic chest pain at rest, and the final diagnosis is myocardial ischemia with objective evidence but without elevation of cardiac biomarkers. For the primary endpoints, the first occurrence timepiont of any one of the above events will be recorded. The follow-up duration is recorded as the interval from baseline CCTA examination to the day of follow-up.

### Secondary Endpoints

Secondary endpoints include cardiovascular death, atrial fibrillation, non-fatal MI, non-fatal stroke, unplanned revascularization, hospitalization for unstable angina, medication adjustment, invasive or non-invasive cardiovascular tests, cumulative radiation exposure from all cardiovascular tests, and total cardiac costs. Medication adjustment includes the increase or decrease of the drug dose and the new addition or discontinuation of medications. For the secondary endpoints, the time of the occurrence for any one of the above events should be recorded.

### Follow-Up

Telephone follow-up will be performed for each enrollee annually by the follow-up team of each medical center until the completion of the 5-year follow-up. The follow-up team in each center includes at least one nurse, one cardiovascular radiologist, and one cardiovascular physician. The follow-up team will first contact the patient via a phone call. If it is unsuccessful, the personal contact will be called for updated information. After documentation of three unsuccessful attempts (on three different days over 1 month) by the follow-up team, a subject will be considered lost to telephone follow-up. If the outcome of this subject cannot be traced through the medical record system, the subject will eventually be deemed to be lost to follow-up. The follow-up team of the core laboratory will randomly select 10% of the subjects from each other medical center for review to confirm the authenticity of the follow-up data.

### Data Collection and Management

Data management and coordination will be performed by the core laboratory. Study investigators in each medical center will collect all text data regarding baseline clinical characteristics, laboratory results, medical/interventional treatments and outcomes and enter them into a web-based electronic case report form. All imaging data will be transmitted to the core laboratory in an anonymous form. A reference number will be assigned to every single enrolled patient. The final China CT-FFR Study-2 database, including text and imaging data, will be constructed from the individual and valid databases, which will be provided by each participating center. Centers providing forms with more than 5% of missing values will be excluded from the final China CT-FFR Study-2 database.

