## Abstract

Coronary artery disease (CAD) is a major contributor to morbidity and mortality worldwide. Myocardial ischemia may occur in patients with normal or non-obstructive CAD on invasive coronary angiography (ICA). The comprehensive evaluation of coronary CT angiography (CCTA) integrated with fractional flow reserve derived from CCTA (CT-FFR) to CAD may be essential to improve the outcomes of patients with non-obstructive CAD. China CT-FFR Study-2 (ChiCTR2000031410) is a large-scale prospective, observational study in 29 medical centers in China. The primary purpose is to uncover the relationship between the CCTA findings (including CT-FFR) and the outcome of patients with non-obstructive CAD. At least 10,000 patients with non-obstructive CAD but without previous revascularization will be enrolled. A 5-year follow-up will be performed. The primary endpoint is the occurrence of major adverse cardiovascular events (MACE), including all-cause mortality, non-fatal myocardial infarct, unplanned revascularization, and hospitalization for unstable angina. Clinical characteristics, laboratory and imaging examination results will be collected to analyze their prognostic value.

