### Exclusion Criteria

1) Refusal to participate.2) <18 years or >80 years.3) Pregnancy or lactation.4) Allergy to iodinated contrast agents.5) Previous revascularization (PCI or CABG).6) Previous cardiac transplantation or valvular surgery.7) Any life-threatening condition or severe co-morbidity.8) Patients with poor image quality studies, unsuitable for further analysis.9) Coronary artery fistula and anomalous origin.10) Complex congenital heart disease.11) Missing data.

During the initial screening stage (conducted by each center), any patients who meet any one of the above 1-7 exclusion criteria will be excluded. The final enrollment will be determined by the core laboratory (Jinling Hospital, Medical School of Nanjing University) after double-checking the data, re-evaluating coronary artery stenosis and image quality.

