## Study Procedures

### Clinical Variables

Baseline clinical characteristics will be obtained through an electronic questionnaire for each participating patient at enrollment, including age, sex, height, weight, diabetes mellitus, hypertension, hyperlipidemia, smoking, drinking, positive CAD family history, clinical symptoms, all patient-reported examinations, medications, and surgeries associated with the cardiovascular disease within 6 months (Tables 1–5). Diabetes mellitus is defined as a history of diabetes mellitus diagnosed or treated by a physician, treated with oral antidiabetic therapy, or an admission fasting blood glucose level ≥126 mg/dl. Hypertension is defined as a history of high blood pressure diagnosed or treated by a physician, treated with antihypertensive therapy, or an admission blood pressure ≥140/90 mmHg. Dyslipidemia is defined as a history of hyperlipidemia diagnosed or treated by a physician, being in treatment with antihyperlipidemic drugs, or admission total cholesterol (TC) ≥200 mg/dl. Smoking/drinking is defined as current smoker/drinker or prior smoker/drinker within the last year. Positive CAD family history is defined as cardiac death or MI in first-degree relatives (<55 years in men or <65 years in women). Chest pain will be recorded and classified as typical angina, atypical angina and non-anginal chest pain according to the site, characteristics and duration of the chest discomfort and its relationship with exercise, and the inducing and relieving factors (20). Typical angina is considered to meet the following three characteristics: (a) constricting discomfort in the front of the chest or in the neck, jaw, shoulder, or arm; (b) induced by excessive physical activity; and (c) relieved by rest or nitrates within 5 min. Patients presenting with two of the aforementioned typical angina features are considered to have atypical angina. Patients presenting with only one or none of the typical angina characteristics are supposed to have non-anginal chest pain. Relevant medications will be recorded as statin, antiplatelet, beta-blockers, angiotensin-converting enzyme inhibitors (ACEI), angiotensin-receptor blockers (ARB), oral hypoglycemic agent, insulin, oral anticoagulation, calcium channel blocker (CCB), and diuretic. In addition, laboratory test results for C-reactive protein, triglycerides, TC, low-density lipoprotein cholesterol (LDL-C), high-density lipoprotein cholesterol (HDL-C), and cardiac enzyme level will be collected, if possible. The Framingham risk score (FRS) will be calculated for subjects with the complete information of age, sex, TC, HDL-C, systolic blood pressure, diabetes mellitus, antihypertensive medication, and smoking status (21). Meanwhile, the Multi-Ethnic Study of Atherosclerosis (MESA) score will also be calculated using age, gender, race/ethnicity, diabetes mellitus, smoking status, TC, HDL-C, antihyperlipidemic drugs, and MI family history (22).

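### Removing whole centres for more than 5% missing values selects the cohort on data completeness, partly on outcome ascertainment, although the plan makes some of those data optional

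*Protocol article*

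**What the plan says.** All places are in the protocol article.

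- **Data Collection and Management**, centre-level rule: "Centers providing forms with more than 5% of missing values will be excluded from the final China CT-FFR Study-2 database". The same section describes what investigators enter on the forms: they "will collect all text data regarding baseline clinical characteristics, laboratory results, medical/interventional treatments and outcomes".
- **Clinical Variables**, on six laboratory items (C-reactive protein, triglycerides, total cholesterol, LDL-C, HDL-C and cardiac enzymes): the list ends "and cardiac enzyme level will be collected, if possible". Incomplete patients are also foreseen there: "The Framingham risk score (FRS) will be calculated for subjects with the complete information of age, sex, TC, HDL-C, systolic blood pressure".
- **Exclusion Criteria**: the last item is "11) Missing data", with nothing further. Centres apply only the first seven criteria at screening ("any patients who meet any one of the above 1-7 exclusion criteria will be excluded"). Criterion 11 therefore falls to the core laboratory, which decides final enrolment after checking the data. The section on CCTA scanning protocols describes the same sequence.
- **Follow-Up**: annual telephone contact for five years, with a defined route by which a subject may end up lost to follow-up.
- **Data Analysis**: a centre-effect analysis across the 29 centres, with stratification, sensitivity analysis or a random centre term if an effect is found.
- **Abstract**: "At least 10,000 patients with non-obstructive CAD but without previous revascularization will be enrolled".

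**The concern.** The centre rule is an explicit instruction about who stays in the database. A later analysis plan could not repair it, because no missing-data method can recover patients who have been taken out of the final database.

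Three things are at stake.

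- **Selection.** Retention depends on how completely a centre fills in its forms. Those forms include outcomes, so it depends partly on what happens after baseline. A centre with weak event ascertainment could be dropped whole, along with its complete patients, their CCTA and their CT-FFR.
- **Internal consistency.** The plan makes six laboratory items optional and accepts some loss to follow-up. It then applies a missingness limit to forms that contain laboratory results and outcomes, with no stated exemption. Criterion 11 raises the same conflict at patient level: read literally, a patient without an optional HDL-C value would be ineligible.
- **Diagnosis of centre differences.** The Discussion already lists selection bias and centre heterogeneity as limitations. The centre-effect analysis is the planned response, but it can only look at centres that remain.

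**Working it through.** **1. Is the rule defined well enough to predict when it acts?** The text does not say whether 5% is counted per form, per variable or pooled over the centre, nor whether an optional test that was not done counts as missing. As an illustration, assume pooling over *F* fields per patient, of which 6 are the optional laboratory items, with every other field complete. The missing share is 6*m*/*F*, where *m* is the laboratory missingness rate. It exceeds 5% when *m* > 0.05 × *F*/6. The article does not give *F*, so a range is shown:

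| *F* (assumed) | *m* needed to exceed 5% |
|---|---|
| 30 | 25% |
| 50 | 42% |
| 100 | 83% |
| 120 or more | cannot be exceeded by laboratory items alone |

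So the rule may be triggered by optional items alone, but whether it is depends on a denominator that is not stated. Missing outcomes would add to the share.

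**2. What would criterion 11 do if it covered the six laboratory items?** With an assumed 10% missing per item, the proportion of patients with at least one item missing runs from 10% (the same patients lack all six) to 1 − 0.90^6 = 47% (items missing independently).

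**3. How much room is there in the centre targets?** The visible rows 1 to 25 of Table 6 give:

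2 × 1,000 + 8 × 500 + 4 × 300 + 11 × 200 = 2,000 + 4,000 + 1,200 + 2,200 = 9,400.

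Rows 26 to 29 are not in the text at hand. The visible targets are in descending order and end at 200, so I assume at most 200 for each unseen row. The total is then at most 9,400 + 4 × 200 = 10,200. Other assumed values of 50, 100 and 150 per row give 9,600, 9,800 and 10,000.

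Starting from the most favourable total of 10,200:

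| Centre lost | Patients left |
|---|---|
| one with target 200 | 10,000 |
| one with target 300 | 9,900 |
| one with target 500 | 9,700 |
| one with target 1,000 | 9,200 |

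Of the 25 visible centres, 2 + 8 + 4 = 14 have a target of 300 or more.

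**4. How likely is it that some centre is lost?** The documents give no rate. If each of the 29 centres had an independent chance *q* of exclusion, the chance of losing at least one would be 1 − (1 − *q*)^29: 44% at *q* = 2% and 77% at *q* = 5%. If exclusion is unrelated to centre size, the expected number left, from totals of 10,000 and 10,200, would be 9,800 to 9,996 at 2% and 9,500 to 9,690 at 5%. These values of *q* are illustrative only.

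**The case against.** The strongest reply has four parts.

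- **The trigger is not shown.** The number of fields is unknown, optional items may not be meant to count, and with 120 or more fields the laboratory items alone cannot exceed 5%. This stands. A reader might infer that the rule is bound to remove centres, but the documents support only that it may.
- **Criterion 11 is an eligibility criterion.** A reader might infer that patients with missing data are deleted after enrolment. The documents do not support that: the core laboratory applies the criterion before final enrolment. It still selects on completeness, and its scope is undefined.
- **No bias has been demonstrated.** Loss to follow-up has its own tracing procedure, and Cox and Kaplan-Meier methods can censor such patients. There is a data check and a 10% review of follow-up data. Dropping a centre need not bias the hazard ratios estimated within the remaining centres. This stands as far as it goes: neither direction nor size of bias can be given. It does not justify discarding complete patients, and it leaves selection tied partly to follow-up quality.
- **Imputation details belong in an analysis plan.** Agreed, and their absence from an article is not the point. The point is the stated removal rule, which would leave an analysis plan with nothing to impute for the lost centres.

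Two further inferences should be resisted. The article does not name the Framingham score as the model that CT-FFR must improve on, so it cannot be said that the compared models will use different patients. Nor does anything suggest that several large centres would fail together; any loss of precision from such a scenario would be hypothetical.

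**Conclusion.** The concern holds in a limited form. The centre rule removes complete patients, selects the cohort on data completeness and partly on outcome ascertainment, and puts excluded centres beyond the reach of the centre-effect analysis. It fits poorly with the plan's optional laboratory items and its acceptance of some loss to follow-up. Criterion 11 adds an undefined patient-level filter that, taken literally, contradicts the optional laboratory items.

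On size, the margin over 10,000 is at most 200 patients, assuming that the four unseen rows of Table 6 are at most 200 each. Losing any single centre of 300 or more would take the analysed cohort below 10,000. A reader might take this as breaking the stated number, but the article gives 10,000 as the number enrolled, and a smaller final database does not contradict that. The text shown gives no power, event-rate or precision basis for 10,000, so no loss of power can be calculated.

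**What to change.** - Replace the centre exclusion with a statement that all enrolled patients from all centres stay in the final database and in the primary analysis.
- Keep 5% as a trigger for data queries. State its unit and denominator, and apply it to a named list of mandatory fields that leaves out the optional laboratory items.
- Limit criterion 11 to named essentials, such as an analysable CCTA dataset.
- Handle missing covariates by multiple imputation, with centre, the event indicator and the cumulative hazard in the imputation model.
- Report the analysis without centres above 5% missing as a sensitivity analysis.

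The cost is a change of wording, a little more analysis work and the retention of some lower-quality data. No new patients or data are needed. The change should be made before the final database is assembled.
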